## Results

Enrollment of study participants is planned to begin in September 2025. We anticipate that the study recruitment will be finalized in 2026 and that the results of the PRIMI trial will be available in 2027. Trial results will be communicated to participating health care units through in-person presentations and written reports. The results will be additionally disseminated through scientific publications, as well as through academic and clinical national and international conferences.

## Discussion

### Expected Findings

The PRIMI trial will examine whether a novel smartphone app (the PRIMI app) can improve diet quality, moderate-to-vigorous physical activity, health literacy, BMI, self-efficacy, and self-rated health in migrant women after childbirth. The PRIMI trial has several strengths, including the randomized controlled trial design and the broad inclusion criteria, which will increase the generalizability of the findings. Furthermore, the development of the PRIMI app incorporated behavior change theory [29] and empirical evidence [15,26,27] and was informed by the target population as well as practical experience from implementers (ie, health care professionals) [49] to foster acceptability and enhance the potential for positive outcomes. In addition, the various types of data collected on participants’ use and experience of the PRIMI app allow for comprehensive investigations into how and why the app may or may not be effective.

However, the conceptualization of migrant women is not straightforward as there is great heterogeneity among groups of people who may share a language but not a culture. Therefore, using language as a proxy for culture may limit the ability to address issues such as values shared within a culture. This is a limitation as the main purpose of targeting is to make messages more effective by incorporating inclusive elements [18]. Nevertheless, focusing on first-generation migrant women without applying major exclusion criteria makes the app available to more women and increases generalizability.

The PRIMI trial has several other limitations that should also be considered. First, the primary outcome measures will be self-reported by the study participants. Although the questions are based on established screening questions from the National Board of Health and Welfare and we have used them in the target group previously [25], they may be subject to recall and social desirability bias. Nevertheless, the use of the categorical answer mode has demonstrated greater validity than open-ended answers [50]. Furthermore, although participants in both the intervention and control groups will self-report outcome measures, there is a risk of detection bias as participants who do not complete the follow-up questionnaire will be contacted by the research staff, potentially revealing their group allocation. While we believe that this procedure outweighs the limitations of a higher attrition rate, we will carefully register cases in which follow-up data were collected via phone. Respondent burden was additionally considered when developing the questionnaires. Finally, the intervention period and follow-up of 6 months may be insufficient to detect long-lasting effects on health behaviors, although many mHealth interventions have had shorter intervention periods [51].

The PRIMI trial will provide novel evidence on whether an mHealth app can promote a healthy lifestyle after childbirth among migrant women. This is highly relevant given the scarcity of comparable studies on similar evidence-based mHealth interventions and the critical importance of the period after childbirth for establishing long-term health behaviors. According to a scoping review on interventions designed for pregnant women or mothers of young children to address risk factors for preventable noncommunicable diseases through health literacy, few interventions used technologies for delivery [52]. In fact, none of the included interventions (N=25) that used a mobile phone app for delivery (n=2) targeted women after pregnancy; they focused exclusively on women during pregnancy [53,54]. Furthermore, this review emphasized that interventions specifically targeting vulnerable populations, including mothers from culturally and linguistically diverse backgrounds, are highly needed [52].

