### Randomization and Blinding

Women will be randomly allocated to the intervention or control group after completion of the baseline measurements in a 1:1 ratio (with random block sizes of 2 and 4 to avoid revealing the allocation sequence). The *blockrand* package in the R software (version 4.5; R Foundation for Statistical Computing) will be used for the computerized random number generator. Randomization will be conducted by a statistician not part of the research team, who will remain separate from the research team members responsible for informing participants of their allocation via phone to conceal the allocation sequence. Participants and outcome assessors will not be blinded to the allocation, but the project statistician and analysts will be blinded to group allocation until completion of the analysis. Although the participants and outcome assessors are not blinded to group allocation, steps have been taken to reduce the risk of performance and detection bias. Thus, the self-reported outcomes will be collected using standardized electronic questionnaires in the preferred languages of the study participants, reducing assessor influence. When necessary, telephone-based data collection will follow a standardized script to ensure consistency across measurements.

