### Intervention Group

Women assigned to the intervention group will receive the PRIMI app in addition to standard care. After randomization, intervention group participants will be contacted via phone by a research team member who speaks Arabic, Somali, English, or Swedish based on the participant’s preference to guide them through the installation of the PRIMI app.

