#### Process Evaluation

User experience data will be collected at the 6-month follow-up by asking intervention group participants about their experiences of the PRIMI app. We will also conduct a process evaluation based on qualitative data collected through interviews with a subsample of women to obtain richer data and a deeper understanding of how the mHealth intervention was perceived and appreciated by the women [42-45].

Furthermore, automatically collected use data will be used to investigate how the app was used by participants, including the number of sessions, the number of registrations, and the time spent on the app.

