A total of 100 women (50 per group) will provide at least 80% power (α=.05) to detect a minimally clinically relevant effect size of a 0.35-SD difference in the primary and secondary outcomes; we simulated trials with different sample sizes and parameter variance (*k*=100 simulations per specification) to find a suitable level whereby there was at least 80% power to detect the relevant effect [48]. It may be argued that smaller effect sizes than this may have limited clinical value, and thus, we consider the sample size sufficient. We aim to recruit 200 women (100 per group) to account for a potential dropout rate of up to 50%. However, we may consider recruiting fewer participants if the actual dropout rate is lower. To prevent dropout, participants will receive a mobile phone SMS text message reminding them about the 6-month follow-up questionnaire a few days before the questionnaire link is sent. Participants who have not completed the questionnaire within a few days will be contacted via phone to be assisted in completing it.

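### Staff who phone late responders at 6 months are not kept unaware of allocation, so assisted self-reports of the primary outcomes could differ by arm; the size is unknown and small if few forms are taken by phone

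*Protocol article*

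**What the plan says.** Randomization and Blinding states that "Participants and outcome assessors will not be blinded to the allocation", while the project statistician and analysts are blinded. The same section names two steps against bias: "the self-reported outcomes will be collected using standardized electronic questionnaires in the preferred languages of the study participants, reducing assessor influence", and, where the telephone is needed, "telephone-based data collection will follow a standardized script to ensure consistency across measurements".

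Statistical Analysis and Power Considerations describes the chase: "Participants who have not completed the questionnaire within a few days will be contacted via phone to be assisted in completing it". Nothing limits this to one arm. The limitations paragraph under Expected Findings accepts a detection-bias risk because "participants who do not complete the follow-up questionnaire will be contacted by the research staff, potentially revealing their group allocation". It prefers this risk to more attrition and adds that "we will carefully register cases in which follow-up data were collected via phone".

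Two other sections bear on what the caller and the woman know. Under Intervention Group, after randomization "intervention group participants will be contacted via phone by a research team member who speaks Arabic, Somali, English, or Swedish" to help with installing the app. Under Process Evaluation, "User experience data will be collected at the 6-month follow-up by asking intervention group participants about their experiences of the PRIMI app".

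**The concern.** Diet and activity are behaviours on which a respondent knows the approved answer. Intervention women know it especially well, because the app gives them weekly traffic-light feedback on a diet score and on activity minutes (Content and Features). When such a woman is helped through the outcome items by a caller who knows her arm, and who belongs to the team that provides the app, she may answer more favourably than a control woman in the same position. Adjustment for baseline does not remove a reporting difference that first arises at follow-up, and blinded analysts cannot see it. It would be counted as an app effect on either primary outcome.

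The app-experience questions add a second route. They go to one arm at the same time point. If they were put before the outcome items, or in the same call, they would disclose the arm and remind the woman what is being evaluated.

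**Working it through.** **What each safeguard does**

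- Electronic self-completion protects women who finish unaided. Late responders who are helped by phone are the exception.
- The script fixes the wording. It does not hide the arm from the caller.
- The register records which forms came by phone. The article attaches no analysis to it.
- No section says that callers work without access to allocation, or that follow-up calls are kept apart from the allocation and installation calls.

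**The plan's own figures**

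The yardstick is the 0.35-SD difference in Statistical Analysis and Power Considerations. The recruitment target reproduces: 100 / (1 − 0.50) = 200. The 50% is a ceiling for dropout, and women who drop out supply no phone data, so it is not an estimate of the phone share. The protocol gives no phone share and no figure for over-reporting.

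**Size of the bias**

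Let p be the share of follow-up forms taken by phone and b the mean over-reporting on those forms, by arm (I = intervention, C = control):

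bias = p_I × b_I − p_C × b_C

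If the shares are equal this is p × d, with d = b_I − b_C. If d is zero as well, there is no bias. The sign is not fixed: with b = 0.2 SD in both arms, p_I = 0.25 and p_C = 0.50, the bias is 0.25 × 0.2 − 0.50 × 0.2 = −0.05 SD, against the app.

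**Chance of a significant result with no true effect**

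Normal approximation, two-sided 0.05, n per group, baseline-to-follow-up correlation ρ:

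SE = √(1 − ρ²) × √(2/n); chance = Φ(bias/SE − 1.96) + Φ(−bias/SE − 1.96)

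Assumed ρ is 0.5 to 0.78; the upper value is where 50 per group gives about 80% power for 0.35 SD. With n = 50, SE = 0.866 × 0.2 = 0.173 at ρ = 0.5, and 0.626 × 0.2 = 0.125 at ρ = 0.78.

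| p (assumed) | d in SD (assumed) | Bias (SD) | Bias / 0.35 | Chance, ρ 0.5 to 0.78 |
|---|---|---|---|---|
| 10% | 0.2 | 0.02 | 6% | 5.2% to 5.3% |
| 10% | 0.5 | 0.05 | 14% | 6.0% to 6.8% |
| 25% | 0.2 | 0.05 | 14% | 6.0% to 6.8% |
| 50% | 0.3 | 0.15 | 43% | 13.9% to 22.4% |
| 50% | 0.5 | 0.25 | 71% | 30.3% to 51.5% |

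Better follow-up does not dilute the bias. With 100 per group, the 50% and 0.3 SD case gives 23.2% to 39.6%, because the standard error shrinks and the bias does not.

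**The case against.** The protocol discloses the risk, weighs it against attrition and gives its reason for phoning. Chasing non-responders is sound where up to half the sample might be lost. This stands as a defence of calling, but it does not explain why the caller needs to know the arm.

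Participants are unblinded, so an intervention woman can over-report on the link as well as on a call. This stands: arm-unaware callers remove only the part that the caller contributes.

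A sensitivity analysis by mode may sit in an analysis plan that is not shown. This stands for the analysis. It applies less to caller access and form order, because the article itself lists its steps against bias and these have to be settled before follow-up data are collected.

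Several stronger readings are tempting, and the documents do not support them:

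- *The protocol does nothing except register phone cases.* It also commits to electronic self-completion and a script.
- *Late outcomes are all dictated to staff.* Women are to be helped to complete the form, and telephone collection is for when it is needed.
- *The app questions prime the outcome answers.* Neither their order nor whether they share a form with the outcomes is stated.
- *The follow-up caller is the person who installed the app.* The article says research staff and does not identify the caller.
- *Only intervention women have a tie to the team.* Both arms learn their allocation by phone from the team, and controls receive the app after follow-up.
- *Mode changes between baseline and follow-up.* The telephone provision is not confined to follow-up.

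**Conclusion.** The point holds as a weakness in the stated conduct of follow-up. Callers who help with self-reported primary outcomes are not kept unaware of allocation, and none of the stated safeguards achieves this. Differential reporting on those calls could bias the arm difference on both primary outcomes.

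The size is unknown. It matters only if both the phone share and the differential over-reporting are substantial. At a 10% share, even 0.5 SD of excess over-reporting gives 0.05 SD and a false-positive chance of at most 6.8% with 50 per group. At a 50% share and 0.3 SD it is 0.15 SD, or 43% of the target effect. All of these inputs are assumptions. A reader might infer that a positive result would be an artefact of the calls, but nothing in the protocol supports that. A change is worth making because it is cheap, costs no follow-up and cannot be made retrospectively.

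**What to change.** Amend Randomization and Blinding, Statistical Analysis and Power Considerations, and Process Evaluation as follows:

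1. Follow-up callers work from a chase list with study number and language but not the arm. Where language cover allows, the caller did not make that woman's allocation or installation call.
2. On the call, the caller first helps the woman complete the link herself and reads items aloud only if that fails.
3. The app-experience questions for the intervention arm open only after the outcome form has been submitted.
4. The planned register is used to report mode of collection by arm. If the analysis plan does not already hold one, add a sensitivity analysis of both primary outcomes by mode, labelled supportive because the self-completed subset is smaller and selected after randomization.

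The cost is a re-ordered electronic form, a call list without allocation and one extra analysis. No extra staff are needed and no call is dropped. The limits should be stated: language cover will sometimes rule out a different caller, a woman may mention the app herself, and over-reporting on self-completed forms is untouched.

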### Conclusions

If the PRIMI app proves effective, it holds potential for large-scale implementation as an evidence-based intervention program at the national level. This is particularly promising given the widespread access to smartphones regardless of socioeconomic background or migrant status.

## Data Availability

Data sharing is not applicable to this paper as no datasets were generated or analyzed during this study.

## Appendix

Multimedia Appendix 1 SPIRIT (Standard Protocol Items: Recommendations for Interventional Trials) checklist.

Multimedia Appendix 2 Primary outcome measures.

## Abbreviations

CONSORT-EHEALTH: Consolidated Standards of Reporting Trials of Electronic and Mobile Health Applications and Online Telehealth
mHealth: mobile health
PRIMI: Promoting Reproductive Health in Migrant Women
SPIRIT: Standard Protocol Items: Recommendations for Interventional Trials
